### Study setting

Potentially eligible children whose parents are interested in the study will be visited either at home or in a clinic, depending on site preference, where informed consent will be sought and infants enrolled/immunised as appropriate by the clinical team. A copy of participant informed consent form is provided as online supplemental material.

### Recruitment and eligibility

Potential participants will be identified and approached using the following recruitment strategies: email, posters, electronic newsletter, leaflets, websites, advertisement in newspapers, radio and on social media and/or mail-out using an approved invitation letter or other approved advertising material to invite them to participate in the study. Parents will be asked to complete a prescreening online questionnaire to assess participants’ eligibility, which will then be assessed by study staff. If interest comes through reply slip, parents will be contacted via phone or email to assess eligibility.

The inclusion, exclusion and temporary exclusion criteria that will be used to screen participants prior to enrolment and before each study visit are compiled in boxes 1–3.

Box 1Inclusion criteria:Infants due to receive their primary immunisations, aged up to 2 months (+ 2 weeks) at first vaccinations.Infants born at ≥ 37 weeks of gestational age.Parent(s) or legal guardian(s) willing and able to follow the requirements of the protocol for the duration of the study.Written informed consent provided by parent or legal guardian aged ≥16 years.

Box 2Exclusion criteria:Prior receipt of vaccines. (Except of Hepatitis B or BCG vaccine).Prior planned receipt of investigational vaccines.Current participation in another research study, except if the study is solely observational.Children of parents who are on the delegation log for this study.A confirmed anaphylactic reaction to neomycin, streptomycin or polymyxin B (which may be present in trace amounts in the tetanus vaccine) and/or kanamycin, histidine, sodium chloride or sucrose (which may be present in trace amounts in the MenB vaccine).Latex hypersensitivity (the syringe cap of Bexsero may contain natural rubber latex).Major congenital defects or serious chronic illness.Presence of an evolving or changing neurological disorder.Presence of central nervous system disease or convulsions in the infant.Bleeding disorder.Confirmed or suspected immunodeficiency.A family history of congenital or hereditary immunodeficiency.Receipt of more than 1 week of immune-suppressants or immune-modifying drugs (e.g., oral prednisolone >0.5 ml/kg/day or intravenous glucocorticoid steroid). Nasal, topical or inhaled steroids are allowed.Administration of immunoglobulin and/or any blood products since birth or planned administration during the study period.History of allergy to any component of the vaccines. Any other significant disease or disorder which, in the opinion of the Investigator, may either put the participants at risk through participation in the study, or may influence the result of the study or the participant’s ability to participate in the study.

Box 3Temporary exclusion criteria:Participants may be temporarily excluded from participating if they have any of the following:Have received BCG and Hepatitis B vaccine within 14 days prior to study vaccines.Have scheduled elective surgery, planned admission or other procedures requiring general anaesthesia within 7 days of receiving a vaccine.In the presence of an acute illness or the presence of fever ≥38ºC, until 24 hours after resolution.Blood sampling will also be postponed for seven days after completion of any antibiotic course to ensure no interference with laboratory tests.

### Trial interventions

#### Investigational medical products

PCV13: PREVENAR13 (Pfizer) a PCV that contains 13 different pneumococcal serotypes and is licensed in Europe. It is part of the UK routine schedule at 3 and 12 months of age. This vaccine is only going to be administered at 3 and 12 months of age. One dose (0.5 mL) will be injected at each vaccination.

PCV15: VAXNEUVANCE (MERCK) is a licensed vaccine to be used in the UK. It is indicated for active immunisation in individuals 6 weeks of age and older. One dose (0.5 mL) will be injected at each vaccination.

PCV20: APEXXNAR/PREVENAR-20 (Pfizer) is a pneumococcal vaccine licensed for use from 6 weeks of age onwards. One dose (0.5 mL) will be injected at each vaccination.

PCV13 will be obtained as part of the routine supply from the UK national immunisation programme.

While PCV15 and PCV20 will be obtained directly from the manufacturers.

Table 3 lists the other non-investigational medical products (IMPs) used in the trial to be given as part of routine infant immunisation schedule.

**Table 3 T3:** Non-investigational medical products

Vaccine	Brand
DTaP-IPV-Hib- Hep B (6-in-1)	Infanrix hexa or vaxelis
MenB	Bexsero
Rotavirus	Rotarix
Hib/MenC	Menitorix
MMR	MMRvaxPro or Priorix

MMR, Measles Mumps Rubella.

### Participant timeline

Enrolment for all participants will begin at 2 months of age, with the final visit occurring at 13 months of age.

### Sample size

The primary analysis of this study will assess the non-inferiority of homologous PCV15/PCV20 schedules to PCV13. Based on prior data, assuming an SD of 0.5 for PCV13 serotypes-specific IgG concentrations on the log₁₀ scale and a non-inferiority margin of 0.67, as recommended by WHO guidelines on clinical evaluation of vaccines,^8^ an effective sample size of 131 participants per arm is needed. After adjusting for an attrition of 10%–15%, the study will recruit a total of 600 participants to achieve 80% power at a two-sided 0.05 significance level. No adjustment for multiple comparisons is made, and non-inferiority will be assessed for each of the 13 serotypes. The overall conclusion regarding non-inferiority will also take the epidemiological data into consideration, as non-inferiority may not be met for all serotypes due to variability.

### Trial procedures

Enrolment into the study will occur when parents have provided consent on behalf of their child and a face-to-face eligibility check has been completed.

### Randomisation

Participants will be randomised to a 1:1:1:1 ratio before their first vaccination visit into four arms to receive PCV vaccine as per the trial design mentioned in table 2. Computer-generated randomisation lists will be prepared by the study statistician at the Oxford Vaccine Group (OVG) using stratified block randomisation. Random block sizes of 4 or 8 will be used. The randomisation lists will be stratified by study site. To ensure allocation concealment, an online randomisation system (REDCap, version 16.0.17) was used, with randomisation lists preloaded into the system.

### Blinding

This is an open-label trial, and neither participants’ parents, investigators, nor laboratory personnel processing the samples are blinded to treatment allocation. However, the pneumococcal serum assays will be performed in an external laboratory, where samples will be analysed using anonymised identifiers with no access to treatment allocation. This ensures that personnel involved in the measurement of immunogenicity outcomes remain blinded, thereby minimising the risk of measurement bias.

### Study visits

A total of five study visits will be conducted for participants enrolled in arm 1, 2 and 4 and 6 visits for participants in arm 3. Table 2 provides an overview of visit details, vaccination schedules and sample requirements for each visit. After obtaining the parents’ written informed consent, all participants will be enrolled in the study at visit 1. A thorough check of the inclusion and exclusion criteria will be undertaken, and the findings, including relevant medical and vaccination history, will be recorded in the database. A physical examination will be performed by a study doctor if a 6–8-week health development review has not been undertaken previously or at the investigator’s discretion if indicated by the medical history. All participants, after receiving IMPs, will be issued a 7-day (days 0–6) eDiary to record temperature and local or systemic reactions.

### Sample collection

Within the study period, there are a few time points where blood and nasal samples are collected. Time points for sampling will depend on the arm the participant is randomised to. There are two time points for blood samples. A maximum of 4 mL, 5 mL and 6 mL blood will be obtained at visit 3, 3A and V5, respectively. A topical anaesthetic cream will be offered prior to each venepuncture.

Nasal samples will be collected at three time points for all participants. Participants randomised to arm 3 will have one additional nasal sample collected. Mucosal lining fluid will be collected using synthetic absorptive matrices, with the strip held in place for 30 to 60 s for better absorption.

### Laboratory testing

Depending on the arm allocation for each participant, two blood samples and three or four nasal samples will be taken throughout the study. Samples will be shipped to a laboratory at a separate site for assessment of serotype specific IgG concentration for PCV13, PCV15 and PCV20. Further details for sampling and laboratory analysis are provided in online supplemental material.

### Data collection

All study documents will be stored safely in accordance with the Data Protection Act 2018 and UK General Data Protection Regulation (UK GDPR). Data collected at each visit will be recorded directly into an electronic data capture (EDC) system (REDCap) hosted on a secure, password-protected server with role-based access controls or onto paper source documents for later entry into the EDC, if direct entry is not available. Paper records will be stored securely and will only be accessible to authorised members of the central study team.

The study database will include audit trails to track data entry and modifications, and regular backups will be performed. Access to data will be restricted to authorised personnel only.

Parents or legal guardians will provide consent for their email addresses to be entered into an electronic diary system, allowing them to complete the diary online. The database incorporates predefined data types and logical constraints to facilitate real-time validation of data. The data management and monitoring teams will conduct continuous oversight of data collection and storage processes throughout the duration of the study.

### E-diary/paper diary

Parents or legal guardians will be provided with an online electronic diary following each PCV vaccination. The diary will be used to record daily temperature measurements and any local and systemic solicited adverse reactions from the day of vaccination through to 6 days postvaccination. Parents will also be provided with a paper diary as a backup in case electronic entry is not possible. Completed paper diaries will be collected at the next study visit, and the data will be entered into the study database by site staff. Paper records will be retained at the study site and stored in the Investigator Site File at study completion.

### Data access

Direct access will be granted to authorised representatives of the Sponsor, host institution and the regulatory authorities to permit trial-related monitoring, audits and inspections. Access to medical records by those outside the direct healthcare team will only occur if consent has been received. This would be for the purpose of clarifying medical history in relation to the inclusion/exclusion criteria and safety reporting.

### Early discontinuation or withdrawal of participants

Parents or legal guardians may withdraw their child from the study at any time and for any reason. The investigator may also discontinue a participant if necessary, including due to ineligibility, protocol deviation, non-compliance, adverse events (AEs), disease progression, withdrawal of consent or loss to follow-up. Data collected prior to withdrawal will remain included in the study analysis. Parents or legal guardians may request destruction of their child’s samples unless they have already been analysed. The reason for withdrawal will be recorded in the Case Report Form (CRF), where available.

### Safety reporting

Safety reporting for the study will commence once the participant has been enrolled following informed consent. It will end following the final study visit (V5). All solicited local and systemic AEs and participant’s axillary temperature, observed by parents or legal guardians will be reported in the eDiary daily for 7 days following vaccination with IMP vaccines. All reported Severe Adverse Events (SAEs) will be recorded over the duration of the study. All other details about safety reporting are provided in online supplemental material.

### Monitoring

The OVG will oversee study conduct and protocol compliance, as delegated by the sponsor. OVG’s Quality Assurance team will perform regular monitoring, as outlined in the study monitoring plan provided in online supplemental material, to ensure the trial is conducted and that the data are accurate and compliant with the protocol, Good Clinical Practice and regulatory requirements

### Interim analyses

There will be no interim analysis.

### Statistical analysis

The primary outcome is the PCV13 serotype-specific IgG 1 month after the booster dose. The geometric mean concentrations (GMC) of IgG will be compared between homologous PCV15 and PCV20 arms and homologous PCV13 arm (as the reference) under the hypothesis:

H0: GMCPCV15/PCV20/GMCPCV13 ≤0.67 or *log*10(GMCPCV15/PCV20)*—log*10(GMCPCV13) ≤−0.174;

H1: GMCPCV15/PCV20/GMCPCV13 >0.67 or *log*10(GMCPCV15/PCV20)*—log*10(GMCPCV13) >−0.174.

The PCV13 serotype-specific IgG concentration will be transformed using logarithmic transformations (base 10) to render a normal distribution. We will test the above hypothesis using the multiple regression on *log*10GMC adjusting for randomisation design variable (site), and the prespecified prognostic factors, including sex, gestational age at birth, birth weight and ethnicity. The adjusted geometric mean ratio will be presented with the two-sided 95% CI. We will claim homologous PCV15/PCV20 arms are non-inferior to homologous PCV13 arm if the lower CI lies above 0.67.

The primary analysis will be conducted on a per-protocol basis among participants whose primary endpoint at D28 postboost is available, as the intention-to-treat analysis is no longer producing a conservative estimation in non-inferiority trials. The modified intention-to-treat analysis will also be conducted as a sensitivity analysis. The primary analysis will be carried out when the primary endpoint of D28 PCV13 serotype-specific IgG data become available.

The extent and pattern of missing baseline and outcome data will be reported. Where possible, reasons for missing data will be explored and documented. If missing primary outcome data are ≤10%, a complete-case analysis will be used; if >10%, multiple imputation under a missing at random assumption will be applied.

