### Protocol amendment affecting PCV schedule

From 1 July 2025, during study enrolment, the national immunisation schedule changed with the second dose of MenB now given at 3 months (previously 4 months) and in consequence the first dose of PCV was to be given at 4 months (previously 3 months). In order to provide some data on the revised schedule for the broader valency PCV vaccines, a substantial amendment was submitted (substantial amendment 3.0: 16 May 2025, approved 24 June 2025) which included comparing the effect of giving the single PCV dose at 3 vs 4 months. This introduced a second randomisation for arms 1, 2 and 4 allocating participants within these arms to receive PCV at 3 or 4 months with the blood sample 1 month after either time point (see online supplemental document: major protocol amendment). The primary endpoint was unchanged by this amendment. At the point of implementation of this amendment 237 infants had already been enrolled into the study. A complete amendment history is provided as online supplemental material.

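### The primary model names site as its only randomisation design variable, although the July 2025 amendment added a second randomised factor and a second enrolment stage; adding both could only help precision, at almost no cost

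*Protocol article*

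**What the plan says.** The Statistical analysis section of the protocol article describes a multiple regression on log10 IgG, "adjusting for randomisation design variable (site), and the prespecified prognostic factors", which it gives as sex, birth weight, ethnicity and gestational age. Site is the only design variable named. It matches the Randomisation section, which describes one randomisation: "Participants will be randomised to a 1:1:1:1 ratio before their first vaccination visit into four arms", with "Random block sizes of 4 or 8 will be used" and "The randomisation lists will be stratified by study site".

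The section on the protocol amendment affecting the PCV schedule describes a later change: "This introduced a second randomisation for arms 1, 2 and 4 allocating participants within these arms to receive PCV at 3 or 4 months". It adds that "At the point of implementation of this amendment 237 infants had already been enrolled into the study", and that "The primary endpoint was unchanged by this amendment". The same section says that the routine schedule also changed, with the second MenB dose moving from 4 to 3 months. Details of the second randomisation are left to a supplement that is not shown.

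**The concern.** The plan adopts a sound principle, which is to adjust the primary comparison for the randomisation design. Since the amendment, that design has more in it than site. Arms 1, 2 and 4 carry a randomised priming age, and enrolment falls into one stage before the change and one after it, with different routine schedules. The covariate list includes sex and birth weight but not a factor that the trial itself randomises.

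Precision is what is at stake. A factor that affects the outcome and is balanced across arms, but is left out of the model, goes into the residual variance. The sponsor treats a timing effect as an open question, since the amendment was made partly to compare the two priming ages. The trial was sized at about 80% power per serotype with little reserve, and any loss would apply to all 26 primary contrasts (13 serotypes, two comparisons).

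**Working it through.** **Inputs from the article.** SD 0.5 on the log10 scale, margin 0.67, 131 evaluable per arm, 80% power, two-sided 0.05, 600 recruited (Sample size); 237 enrolled before the amendment (amendment section).

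**Assumptions, not in the article.** The second allocation is 1:1. The 237 are spread evenly over the arms. The SD of 0.5 holds within a timing group. The timing effect on 13-month IgG is unknown, so a range of ratios from 1.0 to 2.0 is used.

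**1. The plan's own figure.** The margin is log10(0.67) = −0.1739. The normal approximation gives 130 per arm. The noncentral t gives 80.1% power at 131 per arm, so the stated 131 reproduces.

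**2. Share allocated to 4 months.** Enrolled after the amendment: 600 − 237 = 363, and 363/600 = 0.605. Half of that is p = 0.3025, so p(1 − p) = 0.211.

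**3. Cost of leaving timing out.** With d the log10 of the timing ratio, the added variance is 0.211 × d². It is set against 0.5² = 0.25, and the interval widens by √(1 + added share) − 1.

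| Timing ratio | d | Added variance | Residual SD | Wider CI | Power at 131 per arm |
|---|---|---|---|---|---|
| 1.0 | 0 | 0% | 0.500 | 0% | 80.1% |
| 1.25 | 0.097 | 0.8% | 0.502 | 0.4% | 79.8% |
| 1.5 | 0.176 | 2.6% | 0.5065 | 1.3% | 79.1% |
| 2.0 | 0.301 | 7.6% | 0.519 | 3.75% | 77.1% |

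**4. Simulation** (10,000 trials per scenario, second allocation either simple or blocked). At a timing ratio of 1.5, power was 78.5–78.7% without the term and 79.2–79.8% with it. At a ratio of 2, it was 77.6–77.7% without and 79.5–80.3% with. With the true ratio at the margin, the one-sided error without the term was 2.1–2.6% across all scenarios, against a nominal 2.5%.

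**5. Adding a stage effect.** Suppose a 2-fold timing shift and a 1.5-fold stage shift. If they act in the same direction, the added variance is 15.7% and power is 74.1%. If they act in opposite directions, it is 5.5% and 77.9%. The article gives no ground for either.

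**6. Chance imbalance in priming age.** If the second allocation were simple 1:1, the between-arm difference in the share allocated to 4 months has SD √(2 × 0.605 × 0.25/131) = 0.048, a 95% range of about ±9 points. The estimated log10 ratio then moves by at most about 0.017 (10% of the margin) at a timing ratio of 1.5, or 0.028 (16%) at 2. With blocking within arm, this is close to zero.

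**The case against.** The strongest reply is that the present wording is not false. Site is the only stratification factor of the arm randomisation, and that is the randomisation on which the primary contrasts rest. Priming age is a further allocation nested within arms, and stage was never randomised. An arm contrast averaged over a randomised sub-allocation is a valid estimate. This stands, and it limits the point to precision and consistency.

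A second reply is that the loss depends on an effect that the article does not quantify, and is small even for a 2-fold effect. This also stands.

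A third is that the supplement or an unseen analysis plan may already include the factor. It may, but the article prints a covariate list for the primary test, and that list would then need to be brought into line.

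A reader might also infer something stronger: that the comparison is exposed to imbalance, and that per-protocol exclusions could leave different mixes of priming age in two arms and bias the ratio. The documents do not support this. Site-stratified blocks of 4 or 8 keep the arms, and hence the stages, nearly balanced over time. Any imbalance in priming age from the allocation itself is due to chance and is already covered by the confidence interval. An unfavourable gap of 10 points would be a roughly 2% event even without blocking (0.10/0.048 is about 2.1 SD). Nothing in the article suggests that exclusions differ by priming age. Likewise, the 74.1% power above should not be taken as the expected loss, because it needs two assumed effects acting in the same direction.

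**Conclusion.** The point holds as one of precision and consistency. The primary model was not updated for the second randomised factor or for the two enrolment stages. It remains valid without them, with no inflation of the type I error. If priming age affects 13-month IgG by up to 2-fold, leaving timing out widens the intervals by up to about 4% and lowers power at 131 per arm by up to 3 points (80.1% to 77.1%). If neither factor has an effect, nothing is gained by adding them. These figures rest on a 1:1 second allocation, an even spread of the 237 over the arms and a within-group SD of 0.5. It would go too far to say that the intervals are wider than necessary as a matter of fact, or that the comparison is biased. The change is a free improvement.

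**What to change.** In the Statistical analysis section, replace the bracketed site with the following:

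- **Arms 1 v 4 and 2 v 4:** site plus a three-level schedule stratum defined by allocation: not re-randomised; randomised to 3 months; randomised to 4 months.
- **Arm 3 v 4:** site plus enrolment stage (before or after the amendment) only, because arm 3 was not re-randomised.

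The stratum should follow allocation, not the age at which the dose was given. Its first level should be labelled as not re-randomised, not as primed at 3 months, because the article says only that those 237 infants had been enrolled. If the sponsor prefers to leave the terms out, one sentence giving the reason would do.

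The cost is a change of wording and about two degrees of freedom out of roughly 260 per contrast. Making it before the 13-month data are analysed avoids a later choice of covariates.
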